## Abstract

**Background:**

The high incidence combined with the high lethality and bad prognosis of lung cancer highlight the need for psycho-oncological care for both patients and their relatives. While psychological interventions for relatives might be helpful, further research on the impact of specific interventions is necessary. Therefore, this trial aims to evaluate structured psycho-oncological counseling for relatives of lung cancer patients based on the Managing Cancer And Living Meaningfully (CALM) approach compared to usual care. In addition, we explore the impact of psycho-oncological support of relatives on the patients’ mental health outcomes.

**Methods:**

The study is a single-center, prospective, randomized controlled trial with two measurement time points. Relatives of lung cancer patients and, thus, the patients themselves (i.e., dyads) are randomly allocated to the intervention group (IG) or the control group (CG) regardless of their disease or treatment stage. Relatives in the IG receive structured counseling based on the CALM approach (three to six sessions with psycho-oncologists). The CG receives usual psycho-oncological care. In addition, cancer patients in both study arms can request psycho-oncological support (usual care) as needed, but they will not get a specific intervention. Relatives and patients complete assessments at baseline (T0) and after the intervention/6 weeks (T1). The primary outcome for relatives is anxiety. Relatives’ secondary outcomes include depressive symptoms, distress, supportive care needs, and quality of life. Patients’ outcomes include anxiety, depression, and distress. All outcomes are assessed using self-report validated questionnaires. Intervention effects will be evaluated using analysis of covariance (ANCOVA) adjusting for baseline values. Power calculations reveal the need to enroll 200 subjects to detect an effect of *d* = 0.4.

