## Background and rationale

In Germany, every year, more than 55,000 people are diagnosed with malignant tumors of the lung. The annual incidence of lung cancer ranks second among men and third among women compared to all other types of cancer [1]. Lung cancer ranks first among men (22.8%) and second among women (15.8%) of all cancer deaths in Germany. Despite advances in diagnosis and therapy, the 5-year survival rate is only 22% in women and 17% in men, and less than half of patients survive the first year after diagnosis [2].

Cancer is often accompanied by psychological and social stress or mental disorders [3]. Particularly lung cancer patients experience psychological distress due to low survival rates, physical discomfort associated with the disease and treatment, and poor quality of life [4]. A recent meta-analysis shows that nearly 50% of all lung cancer patients show high levels of psychological distress [5]. Furthermore, studies report a high incidence and prevalence of depression and anxiety [6–8]. The prevalence of a major depressive disorder is 14.4%, correlating with poor quality of life, fatigue, and sleep disturbances [9]. Overall, data on psychological burden highlight the need for psycho-oncological support [3].

Cancer is not only a burden for the patients themselves, but it also negatively impacts their relatives’ psychological and physical well-being [10]. However, family members often neglect their own needs by focusing on the disease of their relatives [11, 12]. Because of late diagnosis, rapid progression, and poor prognosis of bronchial cancer, relatives are particularly vulnerable and report higher levels of distress than do relatives of other cancer patients [13, 14]. Some studies show that the relatives’ emotional burden may be even higher than the patients’ [13, 15–17]. In addition, the physical and psychological health of cancer patients and their relatives are interdependent [18, 19]. Psychological support for family members positively in turn affects the patient’s psychosocial outcomes. Lung cancer patients with higher resilience and social support have lower levels of anxiety and depression [20].

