A recent review reported that depression and anxiety disorders and psychological distress are significantly associated with an increased risk of cancer-specific mortality and all-cause mortality in lung cancer patients [21]. There is also evidence of poor survival in patients with metastatic lung cancer and persistent depression [22]. The results highlight the need for treatment and psycho-oncological care for lung cancer patients. Because cancer patients and their family caregivers are affected by their own and each other’s mental and physical health, it seems essential to provide psycho-oncological care to family members when needed. The aim of a holistic treatment should therefore include the support of the relatives to achieve better care. Therefore, psycho-oncological guidelines also recommend the support of relatives and other informal caregivers [23, 24]. A systematic review on psychological interventions for informal caregivers of lung cancer patients examined 22 studies with interventions classified into four categories, i.e., communication-based, coping skill training, multicomponent, and stress reduction. Most of the interventions with various delivery modes showed improved burden, anxiety, depression, stress, overall quality of life, self-efficacy, and coping skills, although not always statistically significant [25]. They conclude that the caregiver’s burden can be alleviated through support and resource creation in the context of psychosocial interventions. However, heterogeneity in design, methodology, interventions, and sample characteristics was challenging, and further research with more rigorously designed studies and robust analyses to establish an evidence‐based practice is required.

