### Sample size calculation

A recent systematic review of interventions for relatives of cancer patients with partly different tumor entities showed heterogeneous results. Many of the included studies showed nonsignificant improvements in outcomes due to insufficient power [25]. Following previous intervention studies with this patient group, which focus on the support of relatives, an effect size of *d* = 0.4 is set [25]. To demonstrate an effect of *d* = 0.4 in the primary outcome (GAD-7) at a significance level of alpha = 0.05 and beta = 0.2 for comparing two independent samples, *n* = 200 relatives are required (100 per group). Due to heterogeneous results and high effort in recruiting this vulnerable group, we plan an interim analysis with *n* = 88 persons (44 per group; sample size showing a medium effect size *d* = 0.6). The trial will be closed if the effect size is *d* = 0.6 or *d* < 0.4. A member of the statistical consulting of the Institute of Clinical Epidemiology, University of Würzburg, supported sample size calculation.

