### Assignment of interventions

#### Randomization and allocation concealment

All participants, i.e., dyads of relatives and lung cancer patients, will be randomly assigned to IG or CG after consent is given and initial questionnaires (T0) are completed.

A block randomization procedure with an allocation ratio of 1:1 is used. A member of the study center (not involved in the study) created the randomization list with computer-generated random numbers linked to the research codes (i.e., a consecutive list of numbers). The research code is used on all questionnaires and medical data instead of the name (pseudonymization; see confidentiality). The list is stored locked at the study center. Research codes are printed on the first questionnaires (T0). Therefore, assignment based on the sequence of the list is determined by the time of receipt of the interest to participate and, consequently, the distribution of the study information, consent form, and questionnaire. Allocation concealment will be ensured, as the study members responsible for enrollment (i.e., study coordinator) will not release the randomization number until the signed consent form and baseline assessments have been completed.

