#### Main research question

The primary and secondary endpoints will be analyzed according to the intention-to-treat principle. Treatment effects (between-group effects) in primary and secondary outcomes will be evaluated using analysis of covariance (ANCOVA) adjusting for baseline values. Statistical significance (*p* < 0.05, two-sided) and effect sizes (*ή*^2^) will be reported for all between-group differences [27]. In addition, within-group effects, including standardized effect sizes (SES) and accompanying 95% confidence intervals (CIs), will be calculated for both study groups.

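### The ANCOVAs name no dyad-partner baseline score: a small optional precision gain for relatives' outcomes, and a plausible unadjusted confounder in the patient analysis

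*Protocol article*

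**What the plan says.** The abstract (Methods) states that "Intervention effects will be evaluated using analysis of covariance (ANCOVA) adjusting for baseline values". Statistical analysis, Main research question, repeats this for the relatives' primary and secondary outcomes. Secondary research question uses the same adjustment for the patients' outcomes. None of the three places names a score from the other member of the dyad.

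Background and rationale holds that "the physical and psychological health of cancer patients and their relatives are interdependent", and later that "cancer patients and their family caregivers are affected by their own and each other", a sentence that goes on to name mental and physical health. Table 2 schedules GAD-7, PHQ-9 and DT at T0 for relatives and for patients; SNCS and CQOLC are for relatives alone. Under Randomization and allocation concealment, dyads "will be randomly assigned to IG or CG after consent is given and initial questionnaires (T0) are completed".

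The patient analysis does not compare randomised arms. It splits patients by whether the relative had fewer than two consultations or at least two. The Control group section says that counselling under usual care follows personal need and the person's own initiative. The Discussion adds that relatives in the intervention group may decline sessions.

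**The concern.** The rationale treats each member's mental state as informative about the other's. Both states are measured before the allocation is known, and the stated models then use only one of them. Two different things are at stake.

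**Relatives' outcomes (randomised comparison).** A prognostic baseline score left out of the model leaves its variation in the residual. The estimate stays unbiased, but its standard error may be larger than necessary. This has some relevance because the Interim analysis section ties closure of the trial to the observed effect size at 88 persons.

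**Patients' outcomes (comparison by consultations received).** The groups form after randomisation, partly through need. If relatives who take two or more sessions differ at T0 in anxiety or distress, and if that state also bears on the patient's T1 score, the comparison mixes the effect of support with the relative's starting point. That is confounding, and the patient's own T0 score need not remove it.

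**Working it through.** **1. The plan's own figure.** Sample size calculation sets d = 0.4 "at a significance level of alpha = 0.05 and beta = 0.2 for comparing two independent samples"; the analysis section makes the test two-sided.
- Normal approximation: n per group = 2(1.960 + 0.842)² / 0.4² = 98.1, so 99 per group, 198 in total.
- Exact noncentral t: 100 per group, 200 in total, power 80.4%.

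The stated 200 reproduces. It takes no credit for any covariate, so it does not depend on this point.

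**2. When the partner's score helps.** Let ρ be the correlation of own T0 with own T1, r the T0–T0 correlation within dyads, and c the correlation of partner T0 with own T1. The article gives none of these; all values below are assumptions. The gain depends on the partial correlation

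p = (c − ρr) / √[(1 − ρ²)(1 − r²)],

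and residual variance is multiplied by 1 − p². With ρ = 0.6 and r = 0.3 the denominator is √(0.64 × 0.91) = 0.763:
- c = 0.18 (partner T0 acts only through own T0): p = 0, no gain.
- c = 0.28: p = 0.10/0.763 = 0.13, variance down 1.7%.
- c = 0.38: p = 0.20/0.763 = 0.26, variance down 6.9%.

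Interdependence alone, which is a marginal association, therefore does not establish a gain.

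**3. Size for relatives' outcomes.** Equivalent extra relatives = 200/(1 − p²) − 200; reduction in standard error = 1 − √(1 − p²). Power is from the noncentral t at N = 200, d = 0.4, ρ = 0.5, with 196 residual degrees of freedom. With own T0 only (197 degrees of freedom) it is 90.2%.

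| p | Variance down | SE down | Extra relatives | Power |
|---|---|---|---|---|
| 0 | 0% | 0% | 0 | 90.2% |
| 0.1 | 1% | 0.5% | 2 | 90.4% |
| 0.2 | 4% | 2.0% | 8 | 91.3% |
| 0.3 | 9% | 4.6% | 20 | 92.6% |

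Estimating one more slope inflates the variance by about (197 − 2)/(196 − 2) = 1.005, or 0.5%, so at p = 0 there is a trivial loss.

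**4. The look at 88.** With 44 per group and ρ = 0.5, the standard error on the d scale is √(0.75 × 2/44) = 0.185. It becomes 0.185 × √0.96 = 0.181 at p = 0.2 and 0.185 × √0.91 = 0.176 at p = 0.3. The cost of the slope is then about (85 − 2)/(84 − 2) = 1.012, which cancels the gain at p = 0.1 (0.99 × 1.012 = 1.002).

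**5. Patient analysis.** Without the relative's T0 score, the bias in the group difference is b × Δ. Here b is the slope of the patient's T1 score on the relative's T0 score, and Δ is the difference in mean relative T0 between the consultation groups, both given the patient's own T0. Randomisation would make Δ zero on average; grouping by consultations received does not. The article gives neither b nor Δ, so no size can be assigned. The direction is also open. Control relatives in greater need may seek more sessions, while intervention relatives who decline may be more distressed or less.

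**The case against.** The strongest reply is that nothing here is wrong. ANCOVA on the baseline value is a standard, valid analysis of a randomised comparison, and a full covariate list commonly sits in an analysis plan, which is not shown. For the relatives' outcomes this stands.

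Three stronger readings are tempting, and the document supports none of them:
- *That the plan adjusts only for the person's own baseline.* The text refers to baseline values without restricting them. Own T0 is the natural reading, but partner scores are neither named nor excluded.
- *That precision is being given away for nothing.* The gain may be zero, as step 2 shows, and the article reports no correlation from which to argue otherwise.
- *That chance imbalance in the partner's T0 score distorts the randomised result.* Such imbalance is larger with 44 per group (standard deviation √(2/44) = 0.21) than with 100 (√(2/100) = 0.14), but the ordinary standard error already allows for it.

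It is also fair to say that a chance-imbalance argument does not describe the patient analysis, whose groups are not the randomised arms. That makes the omission more important there, because the relative's T0 score becomes a plausible confounder. Finally, SNCS and CQOLC have no patient counterpart, so the choice of a patient score for those two models is a convention.

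**Conclusion.** The point holds as a minor one with two parts.

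For relatives' outcomes it is an optional improvement: 0 to 9% of residual variance, or 0 to about 20 of 200 relatives, under assumed partial correlations of 0 to 0.3. The planned comparison is unbiased without it, and the sample size of 200 is unaffected.

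For the patient analysis, omitting the relative's T0 score risks confounding, because the groups depend on sessions taken up and uptake depends partly on need. This rests on the article's own description of usual-care counselling and of interdependence within dyads. Its size and direction cannot be determined from the article. Adjustment would lessen the bias but would not remove it, since unmeasured reasons for taking up sessions remain.

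**What to change.** In Statistical analysis, name the covariates:
- **Relative models:** group, the relative's own T0 score, and the patient's T0 score on the same scale (GAD-7, PHQ-9, DT). For SNCS and CQOLC, name one patient T0 score in advance, for example GAD-7.
- **Patient models:** consultation group, the patient's own T0 score, and the relative's T0 score on the same scale. State that residual confounding remains.
- **Missing partner T0 values:** include them in the multiple imputation already planned.
- **Sensitivity analysis:** keep the own-baseline model for every outcome.

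Fix and date this before the look at 88; the analysts are not blinded, so the covariates should not be open to choice afterwards. The cost is a few sentences and one degree of freedom per model, with no new data or visits.

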**Discussion:**

The study will provide evidence for the effectiveness of the CALM intervention in relatives of lung cancer patients. Furthermore, study results will contribute to a better understanding of the effectiveness of a psycho-oncological intervention for highly impaired cancer patients and their relatives. If the CALM intervention positively affects the relatives’ psychosocial outcome, it may be implemented in routine care.

**Trial registration:**

German Clinical Trials Register DRKS00030077. Retrospectively registered on 26 October 2022.

**Supplementary Information:**

The online version contains supplementary material available at 10.1186/s13063-024-07954-9.

## Background and rationale

In Germany, every year, more than 55,000 people are diagnosed with malignant tumors of the lung. The annual incidence of lung cancer ranks second among men and third among women compared to all other types of cancer [1]. Lung cancer ranks first among men (22.8%) and second among women (15.8%) of all cancer deaths in Germany. Despite advances in diagnosis and therapy, the 5-year survival rate is only 22% in women and 17% in men, and less than half of patients survive the first year after diagnosis [2].

Cancer is often accompanied by psychological and social stress or mental disorders [3]. Particularly lung cancer patients experience psychological distress due to low survival rates, physical discomfort associated with the disease and treatment, and poor quality of life [4]. A recent meta-analysis shows that nearly 50% of all lung cancer patients show high levels of psychological distress [5]. Furthermore, studies report a high incidence and prevalence of depression and anxiety [6–8]. The prevalence of a major depressive disorder is 14.4%, correlating with poor quality of life, fatigue, and sleep disturbances [9]. Overall, data on psychological burden highlight the need for psycho-oncological support [3].

Cancer is not only a burden for the patients themselves, but it also negatively impacts their relatives’ psychological and physical well-being [10]. However, family members often neglect their own needs by focusing on the disease of their relatives [11, 12]. Because of late diagnosis, rapid progression, and poor prognosis of bronchial cancer, relatives are particularly vulnerable and report higher levels of distress than do relatives of other cancer patients [13, 14]. Some studies show that the relatives’ emotional burden may be even higher than the patients’ [13, 15–17]. In addition, the physical and psychological health of cancer patients and their relatives are interdependent [18, 19]. Psychological support for family members positively in turn affects the patient’s psychosocial outcomes. Lung cancer patients with higher resilience and social support have lower levels of anxiety and depression [20].

A recent review reported that depression and anxiety disorders and psychological distress are significantly associated with an increased risk of cancer-specific mortality and all-cause mortality in lung cancer patients [21]. There is also evidence of poor survival in patients with metastatic lung cancer and persistent depression [22]. The results highlight the need for treatment and psycho-oncological care for lung cancer patients. Because cancer patients and their family caregivers are affected by their own and each other’s mental and physical health, it seems essential to provide psycho-oncological care to family members when needed. The aim of a holistic treatment should therefore include the support of the relatives to achieve better care. Therefore, psycho-oncological guidelines also recommend the support of relatives and other informal caregivers [23, 24]. A systematic review on psychological interventions for informal caregivers of lung cancer patients examined 22 studies with interventions classified into four categories, i.e., communication-based, coping skill training, multicomponent, and stress reduction. Most of the interventions with various delivery modes showed improved burden, anxiety, depression, stress, overall quality of life, self-efficacy, and coping skills, although not always statistically significant [25]. They conclude that the caregiver’s burden can be alleviated through support and resource creation in the context of psychosocial interventions. However, heterogeneity in design, methodology, interventions, and sample characteristics was challenging, and further research with more rigorously designed studies and robust analyses to establish an evidence‐based practice is required.

A tool that might be helpful in the psychological support of relatives is the Managing Cancer And Living Meaningfully (CALM) intervention. CALM is a brief, tailored, supportive-expressive psychotherapeutic intervention that intends to treat and prevent depression and end-of-life distress in patients with advanced cancer. It provides a therapeutic relationship and reflective space about four domains: symptom management and communication with health care providers, changes in self and relations with close others, spiritual well-being and the sense of meaning and purpose, and mortality and future-oriented concerns [26]. CALM is feasible and effective in patients with advanced cancer. Patient-identified unique benefits of the intervention are [1] a safe place to process the experience of advanced cancer, [2] permission to talk about death and dying, [3] assistance in managing the illness and navigating the healthcare system, [4] resolution of relational strain, and [5] an opportunity to “be seen as a whole person” within the healthcare system [27]. A controlled study showed the positive effects of CALM on depressive symptoms, coping, and psychological well-being in patients with advanced cancer [28]. However, to our knowledge, no study applied the CALM manual to support relatives. Therefore, we conducted the following study with relatives of patients with lung cancer.

## Objectives

Our study aims to prove the effectiveness of a structured psycho-oncological intervention based on the CALM (CALM intervention) compared to usual care for relatives of lung cancer patients. In a randomized controlled study, we examine the following research questions:

The following are the main research questions:Does a CALM intervention for relatives of lung cancer patients (IG) reduce the extent of self-reported anxiety *(primary outcome*) compared to usual care (CG)?Does a CALM intervention for relatives of lung cancer patients (IG) reduce self-reported symptoms of depression, distress, and supportive care needs while increasing quality of life (*secondary outcomes*) compared to the CG?

We hypothesize that the CALM intervention for relatives of lung cancer patients reduces the extent of reported anxiety among relatives (*primary hypothesis*). In addition, we expect superior effectiveness of the CALM intervention regarding depression, distress, supportive care needs, and quality of life.

As a *secondary research question*, we explore the impact of psycho-oncological support of relatives on the patients’ mental health outcomes.Does the psycho-oncological support of relatives positively affect patients’ levels of depression, anxiety, and distress indirectly?

We expect that a supported and resource-empowered relative has an indirect positive effect on the patient’s well-being.

